### Follow-up

The researcher will assist each patient in outpatient follow-up and data collection at 1, 3, 6, and 12 months (Figure 1). For patients who cannot visit the outpatient clinic for follow-up, follow-up will be completed by video telephone and social media software, and schedule a specific time for the ultrasound examination.

### Sample size and study duration

According to previous studies (27–32) and recent systematic analyses, the 12 month recurrence rate after the thermal ablation of VVs in the lower extremities is approximately 3%–5%. The setting in the OM group is 4% and the non-inferiority threshold *δ* is −6% (17). With a statistical power of 90% and a significant equivalence of 1.7% (one-sided), at least 511 patients (170 in each group) needed to be recruited. However, considering the potential withdrawal rate of 20% and the very low incidence of adverse events in this trial, the total sample size was increased to 600 patients (200 in each group). The patients will be followed up for 12 months, and the study is expected to last for 36 months.

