### Primary outcome

The primary outcome is the recurrence of target VVs at 12 months (21, 22). New recurrence is defined as the postoperative appearance of VVs that did not exist in the VV area in the lower limbs before surgery; primary recurrence is defined as the reappearance of VVs that existed in the VV area before surgery during follow-up. Both types of recurrence are defined as postoperative recurrence.

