### Statistical analysis

Analysis will follow the intention-to-treat (ITT) and per-protocol (PP) principles. Continuous outcomes (AVVQ score, VCSS, VAS score, and CIVIQ) will be analyzed using linear mixed models (LMMs) adjusted for baseline values, center, CEAP class, and time. Non-inferiority will be declared for the AVVQ score at 12 months if the upper limit of the 95% CI for the difference (OM-SM or TM-SM) is <*δ* (2.0 points). Recurrence rates will be compared using Kaplan-Meier survival analysis and Cox proportional hazards models. Complications will be compared using chi-square tests or Fisher’s exact tests. Compliance will be summarized descriptively. Subgroup analyses (e.g., by CEAP class, ablation type) are planned. Sensitivity analyses will be performed to assess the impact of missing data. SPSS version 21.0 will be used. *p* < 0.05 will be considered to indicate significance for superiority analyses.

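### The 6-point recurrence margin used to size the trial is larger than the 4% recurrence rate it is paired with, so meeting it could not exclude any benefit of longer compression that is possible at that rate

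*Protocol article*

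**What the plan says.** The primary endpoint is binary and adverse: "The primary outcome is the recurrence of target VVs at 12 months" (Protocol article, Primary outcome).

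Under Sample size and study duration, the article reports that "the 12 month recurrence rate after the thermal ablation of VVs in the lower extremities is approximately 3%–5" per cent. It then fixes the planning value and the margin together: "The setting in the OM group is 4% and the non-inferiority threshold" is given as −6%, with a literature citation and no further reasoning. The error rates follow: "With a statistical power of 90% and a significant equivalence of 1.7% (one-sided"). The result is "at least 511 patients (170 in each group) needed to be recruited", raised to 600 (200 per arm) for withdrawals. This paragraph does not say which arm is the reference.

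Under Statistical analysis, a non-inferiority rule is written for one endpoint only, the AVVQ score at 12 months (2.0 points), using "the difference (OM-SM or TM-SM"). Recurrence is to be compared by Kaplan-Meier and Cox methods, with no non-inferiority rule stated.

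**The concern.** A non-inferiority margin should mark the largest loss that could be tolerated, and it has to be smaller than the benefit at risk. Here the assumed recurrence rate is 4% and the margin is 6 points. A rate cannot fall below zero, so longer compression cannot save more recurrences than the shorter arm has. At the assumed rate, that saving is smaller than the margin.

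The article asks whether compression duration affects recurrence and expects its results to change guidelines. If non-inferiority at 6 points became the headline on recurrence, one month could be reported as non-inferior although six months had halved recurrence or nearly abolished it.

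**Working it through.** **Inputs** (Sample size and study duration): OM rate 4%, range 3% to 5%, margin 6 points, one-sided α = 1.7% (z = 2.120), power 90% (z = 1.282), 170 per arm before and 200 per arm after the allowance for withdrawals.

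**The plan's own figure.** With equal rates and unpooled variance, n per arm = 2p(1−p)(z_α + z_β)²/δ² = 2 × 0.04 × 0.96 × (2.120 + 1.282)²/0.06² ≈ 246.8, so 247 per arm (741 in total), not 170. The stated 170 does not follow from the stated inputs. A 3% rate at one-sided 2.5% does give 170. That is a separate matter, and the argument below does not depend on it.

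**Reading A: shorter arm tested against SM.** The largest true OM − SM is the OM rate minus 0.
- OM 4%: at most 4 points.
- OM 5% (top of the range): at most 5 points.

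Both are below 6. The hypothesis to be rejected, an excess of 6 points or more, cannot be true at any rate in the stated range. Margin ÷ assumed rate = 6/4 = 1.5.

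**Reading B: 4% is the reference rate.** The comparison arm is accepted up to just under 4 + 6 = 10%. That is 10/4 = 2.5 times the reference and twice the top of the stated range.

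**Chance of meeting the margin under Reading A.** Exact binomial enumeration, OM 4%, margin 6 points, one-sided 1.7%. The article names no test, so two are shown: the Farrington-Manning score test and the Wald limit d + 2.120 × √[p₁(1−p₁)/n + p₂(1−p₂)/n] < 0.06.

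| True SM rate | Score, n = 170 | Score, n = 200 | Wald, n = 170 | Wald, n = 200 |
|---|---|---|---|---|
| 2% | 36.9% | 44.9% | 54.1% | 61.6% |
| 1% | 21.7% | 27.5% | 41.6% | 48.4% |
| 0% | 8.8% | 9.5% | 32.2% | 30.8% |

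An example with the Wald limit: 6/200 in OM against 0/200 in SM gives 0.030 + 2.120 × √(0.03 × 0.97/200) = 0.030 + 0.0256 = 0.0556, which is below 0.06 and passes.

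**Power of 200 per arm at smaller margins**, both arms at 4%, one-sided 1.7%, before dropout: Φ(δ/SE − 2.120), with SE = √(2 × 0.04 × 0.96/200) = 0.0196.

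| Margin | δ/SE − 2.120 | Power |
|---|---|---|
| 6 points | 0.942 | 83% |
| 5 points | 0.432 | 67% |
| 4 points | −0.079 | 47% |
| 3 points | −0.589 | 28% |

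**The case against.** Four points on the other side carry weight.

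- **No decision rule for recurrence is written.** The 6-point figure appears only in the sample-size paragraph, and recurrence gets Kaplan-Meier and Cox analyses. This stands: the article does not say that non-inferiority on recurrence will be declared. It does size the primary outcome for that claim, however, so the threshold is there for readers and authors to use.
- **The direction is inferred.** Shorter minus longer is written for AVVQ alone, and the negative sign does not suit an adverse outcome unless the difference is reversed or put in terms of freedom from recurrence. This stands too. The impossibility belongs to Reading A only. Under Reading B the objection is to the size of the margin.
- **4% is a planning value.** Patients range from C2 to C6, and both new and reappearing varices count as recurrence, so the true rate could be higher. A met margin would then exclude an excess of 6 points or more, which is real information.
- **The margin carries a citation.** That source is not available here, so its clinical basis cannot be judged. The mismatch with the assumed rate can be seen without it.

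A reader might go further and infer that one month cannot fail the test, or that meeting the margin says nothing. Neither is supported. The bound concerns the true difference. In the sample the margin is often missed, and the chance of meeting it falls as the true benefit of SM grows.

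**Conclusion.** The point holds as a mismatch between the margin and the assumed rate. For any OM rate in the stated 3% to 5%, meeting the 6-point margin against SM cannot exclude any benefit of longer compression that is possible at that rate. With 4% as the reference, the margin tolerates almost 10%.

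If SM truly halves a 4% rate, the margin would be met 37–45% of the time (score) or 54–62% (Wald). The figures are 22–28% or 42–48% if SM is 1%, and 9–10% or 31–32% if SM is 0%.

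These figures assume OM at 4%, the stated one-sided 1.7%, 170 to 200 evaluable patients per arm, and a binary comparison of 12-month risks. The choice of test changes them materially, and the article does not fix one. The bound itself needs only the stated rates and margin.

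**What to change.** Keep 600 patients and amend the protocol and analysis plan wording:

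1. Name the reference arm and the direction of the difference for recurrence, with a sign that suits an adverse outcome.
2. Report the 12-month risk difference and risk ratio with confidence intervals for each comparison.
3. Word a met 6-point margin only as: an excess of 6 points or more is excluded.
4. Reserve any claim that a shorter duration is as good for a justified margin below the assumed rate, and state the power that 200 per arm gives at that margin: about 47% at 4 points or 28% at 3, against 83% at 6. These are before dropout. The planned 20% withdrawal would leave 200 × 0.8 = 160 per arm, where power at 6 points is about 73%.

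Barring the claim only when the interval lies wholly above zero would add little. At 200 per arm with Wald limits, a met margin and a 95% interval above zero occur together in about 1.5% of trials if SM is 2% and 7.4% if SM is 1%.

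The cost is wording only, with no extra patients. The downside is a weaker permitted claim and a less favourable stated power.

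### The printed sample size inputs need about 247 patients per group (741 in total), not 170 (511); at 170 per group the power is about 76%, not 90%

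*Protocol article*

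**What the plan says.** The whole calculation stands in one paragraph of the protocol article, under Sample size and study duration.

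- Background: "the 12 month recurrence rate after the thermal ablation of VVs in the lower extremities is approximately 3%–5%".
- Rate and margin: "The setting in the OM group is 4%" and "the non-inferiority threshold *δ* is −6% (17)". The minus sign is a matter of direction; the margin is 6 percentage points in size. No separate rate is given for the three-month or six-month group.
- Power, level and result: "With a statistical power of 90% and a significant equivalence of 1.7% (one-sided), at least 511 patients (170 in each group"). The 1.7% is close to 5% divided by three, although the text does not say so.

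The figure is then raised to 600 (200 per group) to allow for 20% withdrawal. No formula or software is named.

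**The concern.** Every input is printed beside the result, so the result can be checked directly, and it looks too small. At a 4% rate with a 6-point margin, 90% power needs more than 200 per group at one-sided 2.5% already. A stricter level of 1.7% can only raise that.

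Recurrence at 12 months is the primary outcome, and this paragraph is the article's only justification for 600 patients. If the power is overstated, the trial is more likely than its readers are told to end without showing non-inferiority when the durations are in truth equivalent. Such an inconclusive result would then be judged against a 90% that the design does not have. A reader also cannot tell which rate, level or power was intended.

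**Working it through.** **Inputs.** From Sample size and study duration: rate p = 0.04, margin 0.06, one-sided level 0.017, power 0.90, withdrawal 20%. From Randomization and blinding: 1:1:1 allocation. Assumption: the comparator's true rate is also 4%. The article states only the one-month rate, and equal rates are the usual planning assumption for non-inferiority.

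**Attempt to reproduce 170.** The unpooled normal formula is

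n per group = (z₁₋α + z₁₋β)² × 2p(1 − p) / margin²

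With z₀.₉₈₃ = 2.120 and z₀.₉₀ = 1.282:

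n = (3.402)² × 2 × 0.04 × 0.96 / 0.06² = 11.571 × 0.0768 / 0.0036 = 246.8

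That is 247 per group and 741 in total. 247/170 = 1.45, so the requirement is 45% above the stated figure.

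**Other methods at the same inputs** all need more per group: 279 with continuity correction, 299 by Farrington-Manning, 303 for two one-sided equivalence tests.

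**Other rates within 3% to 5%, at one-sided 1.7% and 90% power:**

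| One-month group | Comparator | n per group |
|---|---|---|
| 3% | 3% | 188 |
| 4% | 5% | 203 |
| 4% | 4% | 247 |
| 5% | 5% | 306 |
| 4% | 3% | 313 |

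**Other levels at 4% v 4% and 90% power:** 225 per group at one-sided 2.5%, and 183 at one-sided 5%.

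**What does land near 170.**
- 3% in both groups, one-sided 2.5%, 90% power: 10.507 × 0.0582 / 0.0036 = 169.9.
- 4% in both groups, one-sided 2.5%, 80% power: 7.849 × 0.0768 / 0.0036 = 167.4, so 168.
- 4% against a 6% comparator, one-sided 1.7%, 90% power: 11.571 × (0.0384 + 0.0564) / 0.08² = 171.4, so 172.

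Each of the first two changes two printed inputs. The third needs an unstated rate outside the article's range.

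**Power of the planned sizes.** At one-sided 1.7%, power = Φ(0.06 / √(2p(1 − p)/n) − 2.120). At 170 per group with 4% v 4%: Φ(0.06/0.02125 − 2.120) = Φ(0.703) = 75.9%. A simulation of the same interval gave 75.7%.

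| Evaluable per group | 3% v 3% | 4% v 4% | 5% v 5% |
|---|---|---|---|
| 160 (200 less 20%) | 84.8% | 73.2% | 63.4% |
| 170 | 86.9% | 75.9% | 66.2% |
| 200 (no loss) | 91.9% | 82.7% | 73.7% |

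Exact power of a Farrington-Manning test at 4% v 4% is about 66% with 170 per group and 75% with 200.

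**The case against.** **The comparator rate is not stated, so 247 rests on an assumption.** This is right, and the assumption should be shown. With 4% in the one-month group, moving the comparator across 3% to 5% moves the requirement between 313 and 203. That does not rescue 170. Even the favourable end exceeds it, and it presumes that shorter compression truly gives less recurrence.

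**Only 170 per group is criticised, while 200 will be enrolled.** This is partly right. The chance of missing true non-inferiority is about 24% at exactly 170. For the planned 200 it is about 17% with no loss and 27% with 20% loss. All three exceed the 10% implied by the text.

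**600 patients could still reach 90%.** They do so at the lower end of the range: at 3% v 3% with no loss, 200 per group gives 91.9%. At the stated 4% they do not, and after 20% loss they do not at 3% either (84.8%).

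**The power figures assume a risk-difference test at one-sided 1.7%.** The Statistical analysis section compares recurrence by Kaplan-Meier and Cox models, and gives a non-inferiority rule only for the AVVQ score. That mismatch is real and is a separate matter. The present check asks only whether the printed inputs give the printed number. At one-sided 2.5%, 200 per group at 4% v 4% would still give only 86.5%.

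**A journal article condenses the full protocol.** That may explain a missing formula. It does not explain inputs and a result, printed side by side, that disagree.

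**Conclusion.** The point stands. The stated 170 per group does not follow from the stated inputs. Assuming equal true rates of 4%, the requirement is 247 evaluable per group (741 in total), and 247 comes from the least demanding of the standard non-inferiority methods tried. The claimed 90% power is about 76% at 170 per group, about 83% with all 600 patients evaluable, and about 73% after the article's own 20% withdrawal. At no rate within its 3% to 5% range does 170 per group give 90% power at one-sided 1.7% with equal rates: the figures run from 87% down to 66%. The near matches suggest that inputs from different calculations were mixed, but the article does not allow that to be settled.

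**What to change.** Correct the paragraph in Sample size and study duration.

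1. Name the formula and the assumed rate in every group. If the printed inputs stand, state that 90% power needs 247 evaluable per group, or 741 in total (247/0.8 = 308.75, so 309 per group and 927 in total before 20% withdrawal).
2. If other inputs were used, for example 3% with one-sided 2.5%, print those instead and align the level used in the analysis with them.
3. Restate the power that the planned 600 deliver. For 4% v 4% at one-sided 1.7% this is about 83% with no loss and about 73% with 20% loss; show the 3% to 5% range beside it.

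The cost is one rewritten paragraph and a less favourable power statement. Enrolment need not change, provided that the lower power is stated openly.

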### Randomization and blinding

Eligible, consenting patients will be randomized at a 1:1:1 ratio to one of the following groups: the one-month group (OM group, elastic stockings for 1 month), three-month group (TM group, elastic stockings for 3 months), and six-month group (SM group, elastic stockings for 6 months) using a central, computer-generated, stratified block randomization sequence via a secure randomization-generated web-based system. Patients and physicians cannot be blinded owing to the nature of the intervention (duration visible to the patients). The outcome assessors (Duplex ultrasound technicians, QoL questionnaire administrators) and statisticians will be blinded to group allocation.

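### The total of 600 does not deliver the stated 20% withdrawal allowance: it leaves 480 with complete 12-month data against the plan's own minimum of 511, at a cost of about 2 to 3 points of power

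*Protocol article*

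**What the plan says.** All the figures are in the protocol article under Sample size and study duration.

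- Base requirement: "at least 511 patients (170 in each group) needed to be recruited".
- Allowance: "considering the potential withdrawal rate of 20" per cent, given together with a remark that adverse events are rare.
- Result: "the total sample size was increased to 600 patients (200 in each group").
- Inputs to the base requirement: "The setting in the OM group is 4" per cent; "the non-inferiority threshold *δ* is −6" per cent; "With a statistical power of 90" per cent; and "a significant equivalence of 1.7% (one-sided").

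The Randomization and blinding section sets equal allocation: "Eligible, consenting patients will be randomized at a 1:1:1 ratio". The abstract repeats the total of 600. The recurrence rate in the comparator group is not given; the only other figure is a literature range of 3% to 5% for 12-month recurrence.

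**The concern.** The order of the text makes 511 the number before withdrawal and 600 the number after it. A reader is entitled to conclude that at least 511 patients would remain if one in five withdrew. They would not. At the withdrawal rate the plan itself names, the number with complete 12-month data falls below the plan's own minimum, so the stated 90% power is protected against only part of the expected loss. In a non-inferiority comparison, lost precision widens the confidence interval and makes an inconclusive result more likely.

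**Working it through.** **Inputs** (Sample size and study duration): minimum 511, or 170 per group (3 × 170 = 510); withdrawal 20%; final total 600, or 200 per group; one-month group rate 4%; margin 6 percentage points; one-sided alpha 1.7%; power 90%.

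**1. Can 600 be reproduced from 511 and 20%?**

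- Standard inflation, N/(1 − d): 511/0.80 = 638.75, so 639 (213 per group).
- The common shortcut, N × (1 + d): 511 × 1.20 = 613.2, so 614.
- The increase actually made: (600 − 511)/511 = 89/511 = 17.4%.

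Neither form gives 600.

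**2. What does 600 cover?**

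- 600 × 0.80 = 480, or 160 per group.
- Shortfall: 511 − 480 = 31 in total; 170 − 160 = 10 per group.
- Largest withdrawal that still leaves the minimum: 1 − 511/600 = 14.8%, or 1 − 170/200 = 15.0% counted per group.

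**3. Cost in power, accepting that 170 per group gives 90%**

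For one-sided 1.7%, z = 2.120; for 90% power, z = 1.282; the sum is 3.402. This sum scales with the square root of the group size:

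- 3.402 × √(160/170) = 3.300
- Φ(3.300 − 2.120) = Φ(1.180) = 88%

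The loss is about 2 points.

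**4. Cost in power on the stated inputs**

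Assumption, because the article does not give it: the comparator rate is also 4%. With the unpooled normal approximation, the variance term is 2 × 0.04 × 0.96 = 0.0768, and power is Φ(0.06/√(0.0768/n) − 2.120).

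| n per group | 0.06/SE | minus 2.120 | Power |
|---|---|---|---|
| 170 | 2.823 | 0.703 | 76% |
| 160 | 2.739 | 0.619 | 73% |

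The loss from 170 to 160 is about 3 points. The drop from 90% to 76% is already present at 170, before any withdrawal. It arises because the same formula with the stated inputs needs 0.0768 × 3.402²/0.06² = 246.8, so 247 per group, not 170.

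**5. Sensitivity to the missing comparator rate, at 160 per group**

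The one-month group is held at 4% and the comparator varied over the article's own 3% to 5%. The distance to the margin is 0.06 − (0.04 − comparator rate).

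| Comparator | Variance term | Distance | Distance/SE | Power |
|---|---|---|---|---|
| 3% | 0.0384 + 0.0291 = 0.0675 | 0.05 | 2.434 | 62% |
| 4% | 0.0384 + 0.0384 = 0.0768 | 0.06 | 2.739 | 73% |
| 5% | 0.0384 + 0.0475 = 0.0859 | 0.07 | 3.021 | 82% |

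**The case against.** **The 511 may already include withdrawal, since the text speaks of recruiting that number.** This does not stand. The next sentence raises 511 on account of withdrawal, which would be pointless if the allowance were already inside it.

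**The low rate of adverse events may justify a smaller increase.** The text lists it beside the 20% as a reason for raising the total. It does not lower the withdrawal rate.

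**Recurrence is to be analysed by Kaplan-Meier and Cox methods, so patients who withdraw contribute until they are censored.** This stands in part. The 480 is the number with complete 12-month data, not necessarily the number analysed. The remote follow-up and reminders described elsewhere in the article may also limit losses. But the sample size is built on 12-month proportions with a difference margin, and the plan itself treats withdrawal as lost information by inflating for it.

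**The stronger reading.** A reader might infer that the withdrawal error takes power from 90% to about 73%. The article's figures do not support that. On the same formula, power is already about 76% at the full 170 per group, so about 14 of the 17 points belong to the base calculation. The 73% also depends on a 4% comparator rate that the article never states. Nor is the trial wholly unprotected against dropout, since 600 covers losses up to 14.8%.

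**Conclusion.** The inconsistency is certain and needs no outside figure: 511, 20% and 600 cannot all hold. At 20% withdrawal, 600 leaves 480 with complete 12-month data, 31 below the stated minimum, and full cover would take 639.

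The consequence of this error alone is modest, about 2 to 3 points of power. The lower figure assumes that 170 per group gives 90%. The upper one assumes 4% in both groups, an unpooled normal approximation and one-sided 1.7%. Both treat withdrawn patients as contributing nothing, so they lean towards overstating the loss if censored follow-up is used. The larger gap below 90% is a separate matter of how 170 per group was obtained, and should not be charged to the withdrawal allowance.

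**What to change.** Keep 600 and correct the sentence in one of two ways.

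1. State that 600 covers about 15% withdrawal from 511. The authors should then say why 15% is credible, so that the rate is not simply fitted to the total.
2. Keep 20% and state the power for 480 completers (160 per group). Declare the comparator rate and show a range: about 62% to 82% for a comparator rate of 3% to 5%, with the one-month group at 4% and one-sided 1.7%.

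Make the change in the same revision that corrects the base calculation, because a new base number would supersede 511 and the 639 derived from it. Moving to 639 alone would repair the inflation and leave the base number unexplained.

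The cost is one rewritten sentence and a less favourable published figure. No change to recruitment, design or data collection is needed.
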